## Abstract

**Background:**

Migraine is a chronic neurologic disease that can severely affect the patient's quality of life. Although in recent years many randomised studies have been carried out to investigate the effectiveness of acupuncture as a treatment for migraine, it remains a controversial issue. Our aim is to determine whether acupuncture, applied under real conditions of clinical practice in the area of primary healthcare, is more effective than conventional treatment.

**Methods/Design:**

The design consists of a pragmatic multi-centre, three-armed randomised controlled trial, complemented with an economic evaluation of the results achieved, comparing the effectiveness of verum acupuncture with sham acupuncture, and with a control group receiving normal care only.

Patients eligible for inclusion will be those presenting in general practice with migraine and for whom their General Practitioner (GP) is considering referral for acupuncture. Sampling will be by consecutive selection, and by randomised allocation to the three branches of the study, in a centralised way following a 1:1:1 distribution (verum acupuncture; sham acupuncture; conventional treatment). Secondly, one patient in three will be randomly selected from each of the acupuncture (verum or sham) groups for a brain perfusion study (by single photon emission tomography). The treatment with verum acupuncture will consist of 8 treatment sessions, once a week, at points selected individually by the acupuncturist. The sham acupuncture group will receive 8 sessions, one per week, with treatment being applied at non-acupuncture points in the dorsal and lumbar regions, using the minimal puncture technique. The control group will be given conventional treatment, as will the other two groups.

**Discussion:**

This trial will contribute to available evidence on acupuncture for the treatment of migraine. The primary endpoint is the difference in the number of days with migraine among the three groups, between the baseline period (the 4 weeks prior to the start of treatment) and the period from weeks 9 to 12. As a secondary aspect, we shall record the index of laterality and the percentage of change in the mean count per pixel in each region of interest measured by the brain perfusion tomography, performed on a subsample of the patients within the real and sham acupuncture groups.

**Trial registration:**

Current Controlled Trials ISRCTN98703707.

## Background

Headache, which is one of the most common causes of patients' seeking attention at neurology clinics, is a highly prevalent health problem and one with considerable socioeconomic impact [1-4]. In Spain, the prevalence of migraine is 16.9% among women and 7.4% among men [5], with 60% of patients having a family background of such headaches [6]. This epidemiologic profile is similar to that reported for other countries [7]. Headache can be considered a social pathology, as it is often discapacitating. A population based study in the USA found that most of the cost provoked by headaches was related to days off work and loss of productivity [8]. It has been estimated that routine activities are limited during 78% of migraine attacks [9]. Spain is believed to lose 13 million working days every year because of migraine [10], and its direct and indirect costs amount to 1076 million Euros, of which 65% is accounted for by indirect costs [5].

There is no curative treatment for migraine, but there do exist various options for pharmacological treatment, and the choice of one type or another depends on the frequency of the attacks, their severity, the patient's activity and tolerance to side effects. In Spain it has been estimated that the most common treatment is applied at the moment of the attack (86.6%); the drugs used when a severe attack occurs include non steroidal anti-inflammatory drugs (NSAIDs) (36.7%), tryptans (28.4%), paracetamol (7.7%) and ergotamine derivatives (7.7%). Patients who suffer repeated attacks are recommended the prophylactic administration of medication such as beta blockers, tricyclic antidepressants and antiepileptic drugs [11]. The effectiveness of these treatments, although it has been corroborated by numerous studies, is limited. For severe cases, it has been estimated that one third of patients fail to respond to the administration of tryptans, which moreover are reserved for those patients who suffer the most severe attacks or who been found to respond poorly to NSAIDs. Prophylactic treatment reduces the frequency of attacks by 50%, but requires a gradual increase of the dose applied and it has an objectifiable benefit of 6 months. Prophylaxis, therefore, reduces but does not eliminate the problem and the need for medication against severe attacks [12]. Tolerance to pharmacological treatment is limited, both for therapy for severe cases and for preventive measures. The main side effects in the former case are gastrointestinal disorders (with NSAIDs) or cardiovascular problems (with ergotamine substances and tryptans). Among the side effects arising from chronic treatment are sedation, fatigue, lack of tolerance to exercise, and weight gain. In addition, there are physiological factors such as pregnancy or old age, and pathological ones such as asthma, ischemic heart disease or hypertension, for which the administration of some of these drugs is contraindicated, and this circumstance also affects the applicability of the therapy in clinical practice [12].

Acupuncture is widely used to treat headache, and can be applied as the sole therapy or as part of a more complex treatment programme [13,14]. Despite its popularity, there persists some controversy as to the differentiation between the specific and the nonspecific effects of acupuncture. A Cochrane review published in 2001 [15] concluded that, in general terms, current evidence supports the value of acupuncture as a treatment for idiopathic headaches, but due to clinical heterogeneity and the low methodological quality of the 26 studies included, it was not possible to make direct recommendations for clinical practice. Fundamentally, some forms of acupuncture seem to be beneficial, but it is unclear as to which treatment strategies (acupuncture points, type of stimulation, frequency, etc.) should be favoured.

The three most recent studies published, during the last two years, report conflicting results. Two studies, which can be classified as belonging to the German strategy of assessing the coverage of acupuncture for certain processes, concluded that both verum acupuncture and sham acupuncture (superficial acupuncture at points not considered to be acupuncture points) are more effective than remaining on the waiting list, untreated [13], but that their results did not differ significantly from those obtained by pharmacological treatment [16]. The third study was a pragmatic one that concluded that acupuncture produces a clinically significant improvement in patients suffering chronic headache, especially in the case of migraine, compared with conventional treatment; moreover, it leads to decreased consumption of medication, visits to the GP and days off work [14]. Endres et al., in a recent review of the subject, concluded that acupuncture treatment for 6 weeks is not inferior to preventive pharmacological treatment for 6 months, but that the use of acupuncture at specific points, needle stimulation and the depth of the puncture are not as important as had previously been thought [17].

The single photon emission computed tomography (SPECT) of brain perfusion is a technique that obtains three-dimensional images of the cerebral distribution of a radiopharmaceutical, reflecting regional brain perfusion [18,19]. SPECT is less expensive than other techniques, is more widely available and is of more general clinical application; moreover, it may enable a semiquantitative analysis of the images [20]. Numerous studies have been made of regional cerebral blood flow (rCBF) in patients with migraine, and hypoperfusion has been found in many cases, with asymmetries in others [21-27]. Indeed, some authors have correlated the abnormalities observed with the severity of the attack [25]. Few studies have made use of brain perfusion SPECT to examine the effects of acupuncture. Lee et al. studied the cerebrovascular response to traditional acupuncture among patients suffering an obstruction of the middle cerebral artery, and compared the results obtained with those produced among 8 healthy volunteer control subjects. Among the patients, there were focal increases in rCBF in the hyperperfused regions that surrounded the ischemic injury, and also in the ipsilateral or contralateral sensory-motor cortex, while the controls presented multiple sites with raised rCBF in each hemisphere, thus showing that among the patients acupuncture produced an activation of neurons that are viable and undergoing cerebral reorganization [28]. Wang and Jia studied the effects of acupuncture on the rCBF of 9 patients with cerebrovascular disease, and on that of 11 healthy subjects, finding significant differences in the cerebral cortex and the contralateral thalamus, in the ipsilateral basal ganglia and in the cerebellum [29]. Newberg et al. investigated changes in rCBF associated with the analgesic effect of acupuncture in 7 patients with chronic pain, and compared these effects with those found in 5 healthy controls. Baseline studies of the thalamus of patients suffering pain presented significant asymmetries, in comparison with the controls. This asymmetry became normalized or inverted after acupuncture. These authors also found significant correlations with changes in the activity of the prefrontal cortex and in the sensory-motor ipsilateral area [30]. Ha-Kawa et al. described the changes in rCBF induced by acupuncture among 3 patients with dystonia, and related these changes to the action of acupuncture on the central nervous system [31].

Acupuncture produces complex changes in the areas of the brain concerned with pain transmission and perception, although the specific details of these effects have yet to be established. The use of neuroimaging techniques enables us to observe changes in cerebral cortical perfusion related to the type of acupuncture applied (verum or sham), and to determine the existence of specific or nonspecific patterns of cortical activation [32].

Summing up, the disparity in results obtained, depending on how the technique is applied, on the diverse therapeutic strategies possible with acupuncture, and on the need to attempt to measure the specific and the nonspecific effects of the technique, led us to design this randomised controlled pragmatic study aimed at investigating the effectiveness of acupuncture applied in primary healthcare centres for patients suffering migraine. Our goals are: a) to assess the effectiveness and safety of acupuncture in the context of standard clinical practice; b) to derive an economic evaluation of the technique; c) to determine the specific and nonspecific effects of the intervention in the study; and d) to examine changes in brain perfusion using SPECT tomography to examine the consequences of the different interventions.

## Methods

### Design

Randomised controlled multicentre pragmatic study, with three arms, to compare the effectiveness of the individualized active acupuncture (Group A), minimal acupuncture (in locations not corresponding to acupuncture points, in different metamers and at a depth of less than 3 mm) (Group B) and conventional treatment (Group C). The patients will be blinded to the two acupuncture treatments. These patients will be assessed and the results analysed by professionals blinded with respect to the allocations of the different treatments. A stratified randomised subsample of groups A and B will be given a SPECT tomography in order to determine possible changes in the cerebral vascular flow provoked by the two different types of acupuncture applied. The duration of the study, per patient, will be 28 weeks, four of which will be prior to randomisation (baseline), followed by 8 weeks of treatment and then 16 weeks' follow up.

### Study period

January 2008-December 2010

### Study subjects

General practitioners at the three primary healthcare clinics taking part in the study, belonging to the public healthcare system in Andalusia (at Armilla, Valle de Lecrín and Ugíjar, all in the province of Granada), will identify potentially eligible patients with migraine symptoms. An independent assessor will interview the participants, perform the screening and instruct the patients in how to complete the headache diary (to be filled in over a period of 4 weeks). The patients will be informed about the procedures of the study and will be requested to sign the informed consent form. They will also be informed about the possible risks associated with the different types of acupuncture (infection, fainting, bruising) and told that that they may end their participation in the study at any time, with no type of penalty or loss of benefits to which they would otherwise be entitled. Although only a subsample will be given the SPECT diagnostic test, all the patients included in the study will be required to sign their informed consent to this test.

The patients included must be at least 18 years old, diagnosed with migraine, in accordance with the principles of the International Headache Society [1] and the recommendations for clinical trials published by the same Society [33], with or without aura, with a frequency of migraine attacks of 2–6 times per month, with a minimum chronicity of one year, the onset of symptoms at an age of less than 50 years, having completed the headache diary, and have signed their informed consent. Criteria for exclusion will include acupuncture during the 12 previous months, incapacity to distinguish between tensional headache and migraine, secondary headaches, contraindication to acupuncture (pregnancy, generalised dermopathy, treatment with anticoagulants, thrombocytopenia) or to the performance of SPECT techniques (cerebrovascular accident, traumatic brain injury, alcohol or drug abuse, severe psychiatric disorders) and inability to complete the questionnaires or to reply to the assessor's questions.

The ethical validity of this study has been assessed and approved by the Andalusian Regional Committee for Clinical Trials, following approval by the Research Committee corresponding to each of the participating centres. The study design complies with the fundamental principles set out in the Helsinki Declaration, as revised in Tokyo (2004), as well as those of the Council of Europe Convention on human rights and biomedicine, and the requirements of Spanish law regarding the field of biomedical research, the protection of personal data, and bioethics. All patients must sign the form of informed consent to clinical research procedures. During the course of the study, audits will be carried out as considered necessary by the corresponding Committee for Research Ethics and by the Quality Control Committee responsible for the centre in question, these being independent of any external audits (by the source of research funding) that may be required.

### Randomisation and treatment allocation

Sampling will be by consecutive selection, in accordance with inclusion-exclusion criteria, over a period of 24 months until the predetermined sample size has been obtained. Randomised allocation to the three arms of the trial will be carried out using an appropriate computer program (EpiDat v 3.1), in a centralised way (by the Research Unit at Hospital Costa del Sol, Malaga), following a 1:1:1 distribution (verum acupuncture: minimal acupuncture: conventional treatment), with a sequence for each clinic in blocks of 9. Secondarily, one patient in three will be randomly selected from each of groups A and B to be given a SPECT brain perfusion study. Neither the centres nor the doctors participating in the trial will take part in the randomisation procedure, and the sequence of the latter will remain concealed until the completion of the trial. The patients who fulfil the criteria for inclusion and who give their informed consent will be included in the trial. After each patient's inclusion, his/her GP will contact the randomisation centre, where the patient will be registered, and the doctor will be told, by phone and by fax, which of the three arms of the trial the patient has been allocated to. This procedure guarantees that the randomisation process will not be influenced by the doctor participating. We shall endeavour to ensure that all participants begin the trial with the same expectations of effectiveness; accordingly, the initial information provided to the patient will state that all the treatments provided in the course of the trial are effective [13,14,16].

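### A single fixed, published block of 9 per clinic with arms disclosed to clinic doctors makes some allocations deducible, so the assurance that the doctor cannot influence randomisation is too strong

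*Protocol article*

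**What the plan says.** All of this is in the protocol article.

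- **Scheme.** Under Randomisation and treatment allocation, allocation is generated centrally, "following a 1:1:1 distribution (verum acupuncture: minimal acupuncture: conventional treatment"), "with a sequence for each clinic in blocks of 9". No other block size is given. Study subjects names three clinics.
- **Who asks and who learns the answer.** After inclusion, "his/her GP will contact the randomisation centre", and "the doctor will be told, by phone and by fax, which of the three arms of the trial the patient has been allocated to". Data compilation adds that the physician giving the treatments controls the allocation information and liaises with the randomisation centre.
- **Who is enrolled.** The abstract describes patients "for whom their General Practitioner (GP) is considering referral for acupuncture".
- **Safeguards.** Patients are taken consecutively. An independent assessor does the screening. Consent and the 4-week diary are required for inclusion, which comes before the call. Of the list, the article says that "the sequence of the latter will remain concealed until the completion of the trial".
- **Assurance.** "This procedure guarantees that the randomisation process will not be influenced by the doctor participating".

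**The concern.** Concealing the list hides future assignments only while they cannot be worked out from past ones. With a constant block size that anyone can read in the article, and with arms disclosed as they are issued, the end of a block can be deduced by someone who has kept count. Needling versus no needling cannot be hidden at a clinic in any case, because group C has no sessions.

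The GP identifies candidates and makes the call, and the patients are people for whom that GP already has acupuncture in mind. If a call were held back or brought forward because the next slot was known to be control, or known not to be, the arms would differ in prognosis. The verum–control comparison is open and rests on a patient-kept diary. The planned regression adjusts for baseline level, pain intensity, frequency, age and sex, but not for whatever else the GP knows about the patient.

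**Working it through.** **Inputs.** Block of 9, ratio 1:1:1 and three clinics (Randomisation and treatment allocation; Study subjects); 24 months of recruitment (Randomisation and treatment allocation); 72 per group, 270 in total, 20% withdrawal and a target of 1.6 days (Sample size).

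**The plan's own figure.** 3 × 72 = 216, and 216 / 0.80 = 270, which reproduces. 270 / 9 = 30 blocks. The article gives no figure for predictability.

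**Certain places per block.** For someone who knows the boundaries and all earlier allocations at the clinic, a place is certain when all the places left belong to one category. With categories of size n_g, the expected number per block is Σ_k Σ_g C(n_g, k) / C(9, k).

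- *Only one named arm left:* 3/9 + 3/36 + 1/84 = 3/7 = 0.429 per block.
- *Exact arm, sizes (3, 3, 3):* 3 × 3/7 = 9/7 = 1.286 per block. Divided by 9 this is 1/7 = 14.3%, and 270/7 is about 39 patients.
- *Certainly needled (no control place left):* 6/9 + 15/36 + 20/84 + 15/126 + 6/126 + 1/84 = 1.5 per block, or 16.7%.
- *Certainly control:* 3/7 per block, or 4.8%.
- *Needling versus control, together:* 27/14 = 1.929 per block. Divided by 9 this is 3/14 = 21.4%, and 270 × 3/14 is about 58 patients.

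Simulation agrees with both rates. The best guess of the exact arm is right 53% of the time, against 33% by chance.

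**With partial knowledge.** As an illustration, suppose a GP knows the boundaries but sees a random share of the clinic's allocations.

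| Share seen | Exact arm certain | Needling versus control certain |
|---|---|---|
| 100% | 14.3% | 21.4% |
| 75% | 2.5% | 7.8% |
| 50% | 0.2% | 2.1% |

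The number of GPs per clinic is not stated, so the share that applies is unknown.

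**Bias if only the certain slots are exploited.** Let the doctor enrol patients whose expected change is d days better when the slot is certainly needled, and d days worse when it is certainly control.

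- Of 6 needled places per block, 1.5 are affected: +(1.5/6) d = +0.25 d in verum, and the same in sham.
- Of 3 control places, 3/7 are affected: −(1/7) d = −0.143 d.
- Verum minus control: 0.25 d + 0.143 d = 0.39 d. Verum minus sham: 0.

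The documents give no value for d, so it is assumed: d = 0.25 gives 0.10 day, d = 0.5 gives 0.20 day (0.20/1.6 = 12% of the target) and d = 1 gives 0.39 day.

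**Room to act.** With equal recruitment across clinics, 270 / 24 / 3 = 3.75 patients per clinic per month, so a block lasts 9 / 3.75 = 2.4 months.

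**The case against.** The strongest reply is that the article does not give the enrolling GP the knowledge these rates need. Each GP is told the arm of his or her own patient. The treating physician holds the allocations, but nothing says that this physician is the caller or shares a tally. That stands. A reader might infer that one assignment in seven is known in advance to the enrolling doctor; the text does not support this, and the figure is a ceiling.

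A reader might also take a larger bias, 0.69 × d, from a doctor who steers at every imbalance in the remaining places. That rule means selecting on prognosis at about 77% of assignments, in both directions and with full knowledge. Nothing in the article suggests such conduct, and varying the block size would barely change the figure, so it is not the right measure of this weakness.

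The safeguards also count. Consecutive selection, independent screening, and consent and diary completion before the call all narrow the scope for steering. The baseline diary must cover the four weeks immediately before the trial (Results measures), which limits how long a call can be held. Baseline adjustment removes part of any prognostic difference. None of these fixes the order or timing of calls, so they reduce the risk without removing it.

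Finally, the assurance can be read as covering only generation of the list, and in that sense it is true. It is too strong if read to cover which patient is put forward for which slot.

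**Conclusion.** The point holds as a modest design weakness. A single fixed, published block of 9 per clinic, with arms disclosed to clinic doctors and a visibly unneedled control group, leaves at most 14.3% of assignments certain as to arm and at most 21.4% certain as needling versus control. These ceilings assume knowledge of the block size, the block boundaries and all earlier allocations at the clinic.

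The bias from exploiting the certain needling-versus-control slots is at most about 0.39 × d for verum versus control, or 0.10 to 0.39 day for an assumed d of 0.25 to 1, before any baseline adjustment. There is none for verum versus sham. The arithmetic is firm. The practical effect is not: nothing in the article shows that steering will occur. What the article cannot support is its unqualified assurance that the doctor has no influence.

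**What to change.** In the central list, replace the constant block with sizes drawn at random within each clinic, for example 6, 9, 12 and 15. Withhold the sizes from clinics and from publications until enrolment ends. Replace the guarantee with a plain description: the list is generated and held centrally, and an arm is released only after the patient has been included and registered.

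**Gain.** In simulation, for someone who knows the possible sizes and all earlier allocations but not the boundaries, assignments certain as to arm fall from 14.3% to about 1.3%, and those certain as needling versus control fall from 21.4% to about 2%. Probabilistic guessing hardly changes: the best guess goes from 53% to 51%, and the any-imbalance bias from 0.69 × d to 0.63 × d. The change removes certainty, not guessing.

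**Cost.** A new list at the randomisation centre and a sentence or two of text, with no extra patients or procedures. If a block of 15 is left open, the arms at a clinic could differ by up to 5 patients (15/3) rather than 3 (9/3).

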### Interventions

The treatment strategies with verum and with sham acupuncture were developed by means of consensus with experienced acupuncture practitioners. All the patients will be allowed to take symptomatic medication to treat headache episodes if necessary, and to continue taking the medication to prevent migraine attacks, following their GPs' recommendations and those of the Headache Study Group of the Spanish Neurological Society [34].

The two groups will receive a total of 8 acupuncture sessions (at a rate of 1 session per week), each lasting 30 minutes, comprising the technique described below and at the locations specified. The acupuncture needles will be sterile, single-use, model S-J2030, made by Seirin Corporation (Shizuoka, Japan) in accordance with EC regulations.

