#### A) Verum acupuncture

Individualized treatment on the basis of diagnosis in accordance with traditional Chinese medicine (TCM), which the acupuncture physician may modify in accordance with the evolution of the patient's symptoms. The TCM diagnosis, evolution, points and techniques applied should be recorded in the DRB.

The doctors responsible for the treatment (specialists in acupuncture with a minimum training of 600 hours and a mean experience of 5.7 years) will insert sterile, single-use filiform acupuncture needles, with a length of 10–30 mm and a diameter of 0.20 mm, with the aid of a guide tube at each of the points, after first disinfecting the skin and with the patient in decubitus. The puncture will be made in accordance with the standards of TCM, to a depth of 1–3 cm, depending on the points selected. The insertion will be followed by stimulation performed with bidirectional rotation actions of the needle sheath in order to produce the sensation known as *Deqi*, commonly described as a sensation of irradiation. The needle will be maintained in place for 30 minutes, with 1–3 manipulations per session.

Any adverse reaction or side effect should be recorded in the DRB, with a detailed description, and stating the date of occurrence.

The time dedicated to the patients allocated to each of the groups should be identical. Similarly, the same time should be devoted to pre and post session evaluations.

The patients randomly selected for the SPECT diagnostic test will be given their first session at the Nuclear Medicine Department of the Virgen de las Nieves Hospital. The remaining sessions, as well as those applied to the other patients, will be performed at the healthcare centres participating in the trial.

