### Data compilation and analysis

#### Data compilation

A referral form has been drawn up, to be filled in by the GP requesting inclusion in the trial of patients who fulfil the selection criteria. A data base will be designed for the electronic storage of the variables recorded in the purpose-built (physical) data record book (DRB). This database (CRDD) will be kept at the analysis centre (in the Research Support Unit, Hospital Costa del Sol, Marbella. Malaga), which will be independent of the randomisation section. Each participating centre will have a duplicate of the structure of the CRDD, together with a codebook containing the definitions and operative characteristics of all the variables. This information will be compiled within an overall file containing the data for all the variables addressed in this trial, both in the user-controlled formats and in those determined by direct observation. These data will be recorded weekly in the CRDD and sent, in coded form, to the analysis centre for safekeeping. Neither the DRB nor the CRDD will identify the group to which the patient is allocated. This information will be controlled by the physician carrying out the treatments, and who will be responsible for liaising with the randomization centre. An external assessor will record all the information except that which is reserved for the medical staff, and will manage all aspects of the distribution of the patients; nevertheless, this assessor will be blind, at all times, to the treatment actually given to each patient. Every two weeks, the analysis centre will perform a quality control exercise on the data received.

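### The protocol's sections disagree on who learns verum or sham: as written the GP is told, and needling data that reveal the arm pass to analysts described as blinded

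*Protocol article*

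**What the plan says.** All references are to the Protocol article.

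- **Randomisation and treatment allocation.** "After each patient's inclusion, his/her GP will contact the randomisation centre", the patient is registered there, and "the doctor will be told, by phone and by fax, which of the three arms of the trial the patient has been allocated to". The sequence is generated centrally, "with a sequence for each clinic in blocks of 9", and "the sequence of the latter will remain concealed until the completion of the trial".
- **Data compilation.** On the group allocation: "This information will be controlled by the physician carrying out the treatments, and who will be responsible for liaising with the randomization centre". On the data record book (DRB) and the database built from it (CRDD): "Neither the DRB nor the CRDD will identify the group to which the patient is allocated". The same section says the DRB variables are stored in the CRDD, entered weekly, sent in coded form to the analysis centre and checked there every two weeks.
- **A) Verum acupuncture.** "The TCM diagnosis, evolution, points and techniques applied should be recorded in the DRB".
- **Interventions.** Patients in all arms may use symptomatic drugs and "continue taking the medication to prevent migraine attacks", on their GP's advice. Under C) Conventional treatment, the GP prescribes the treatment.
- **Design.** Blinding is claimed for patients (between the two acupuncture types), for those who assess them and for those who analyse the results. GPs are not named.
- **Statistical analysis.** Groups are to be anonymised. Sham is the reference for baseline imbalance, and group C is the reference for the outcome tests and regression.

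**The concern.** Verum against sham is the only contrast protected by patient blinding, and it carries the stated aim of separating specific from nonspecific effects. The primary outcome is counted from a diary that the patient completes. Two features weaken that protection.

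First, the GP needs to know at most whether a patient is having acupuncture. Telling the GP verum or sham serves no purpose in delivering treatment. It gives the distinction to someone who sees the patient in ordinary care and advises on acute and preventive drugs. Change in that drug use is itself a secondary outcome. A chance remark to the patient, or medication advice that differs by arm, would act on exactly the contrast that blinding is meant to protect.

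Second, a record of where and how the patient was needled is in effect a record of the arm. If it travels to the analysis centre during the trial, leaving out a group variable does not keep the analysts blind.

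**Working it through.** The plan states no figure on this point, so there is none to reproduce. Steps 1 to 4 compare the sections; step 5 is a bounded side calculation.

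**1. Who learns the arm.** Randomisation and treatment allocation names the GP as the caller, and the next clause says the doctor is told one of three arms. The only doctor just named is the GP. Data compilation makes the treating physician both the holder of the information and the contact with the randomisation centre. For the two acupuncture arms these are different people: the needling is done by acupuncture specialists, described under A) Verum acupuncture. The two sections cannot both describe the same information flow.

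**2. What the GP does with it.** The GP does not needle. Under Interventions the GP's advice governs symptomatic and preventive drugs in all arms. A route from knowledge of the arm to co-treatment, and to the patient, therefore exists as the text stands.

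**3. What the DRB reveals.**
- Verum: individually chosen points, needled 1–3 cm deep, with stimulation to obtain Deqi.
- Sham: five fixed bilateral dorsal and lumbar non-acupuncture points, less than 3 mm deep, no attempt at Deqi.
- Control: no needling.

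The points and techniques fields therefore separate all three arms. The TCM diagnosis alone may not, because Results measures describes a baseline examination by TCM norms without limiting it to one arm. The chain is then: points and techniques enter the DRB, DRB variables enter the CRDD, and the CRDD goes to the analysis centre. This contradicts the statement that neither identifies the group. Coding patient identity does not help, because the clinical content gives the arm.

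**4. Reference groups.** An analyst who sets sham as reference for one analysis and group C for another knows two of three labels, and the third follows. The section does not say who sets the references.

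**5. Predictability in blocks of 9 (upper bound).** Inputs: blocks of 9 per clinic and 1:1:1 allocation, so 3 of each arm; 270 patients (Sample size). Assumption not in the document: one person knows the block size and every earlier arm at that clinic.

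- An allocation is certain when all remaining places in the block belong to one arm. Expected number per block = P(last 1 alike) + P(last 2 alike) + P(last 3 alike) = 1 + 2/8 + (2/8)(1/7) = 1.286. Share: 1.286/9 = 14.3%.
- At least one arm is exhausted when the last k places lack an arm. Summing over k = 1 to 6: 1 + 1 + 57/84 + 45/126 + 18/126 + 3/84 = 3.214. Share: 3.214/9 = 35.7%, so 35.7 − 14.3 = 21.4% have exactly one arm ruled out.
- Over 270/9 = 30 blocks: 30 × 1.286 ≈ 39 certain allocations.

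**The case against.** Much can be said for the protocol.

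- **GP blinding is never claimed.** A GP who knows the arm breaks no stated promise, and the trial is declared pragmatic. This stands: the GP's knowledge is an avoidable weakness, not a contradiction of a blinding statement.
- **The doctor might be the acupuncturist.** A) Verum acupuncture also calls the acupuncturists doctors, and Data compilation supports that reading. This softens the certainty about who is told, but it confirms that the two sections need reconciling.
- **A reader might infer that allocation concealment fails.** The document does not support this. Allocation is central and released after inclusion, one patient at a time. Each GP is told about his or her own patients, an independent assessor screens, and a 4-week baseline diary precedes randomisation. Learning a past allocation is not seeing the sequence, and nothing says anyone at a clinic knows all earlier arms.
- **A reader might infer that the assessor is unblinded.** The assessor does not record what is reserved for medical staff, so assessor blinding is exposed to risk but not shown to fail. How the DRB is partitioned may also be set out in a fuller protocol. That does not remove the conflict over what reaches the analysis centre.
- **Differential drug use would be visible.** Medication is recorded in the diary. That would help detect co-treatment differences, but adjusting for drug use that arises after randomisation would not reliably restore the blinded contrast.
- **Reference groups can be set by someone outside the analysis.** True, so naming them weakens the anonymised analysis without proving that it is unblinded.

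**Conclusion.** The point holds in a limited form. Two conflicts are plain in the text: who learns the allocation (Randomisation and treatment allocation against Data compilation), and whether the DRB and CRDD reveal the group (A) Verum acupuncture against Data compilation). Followed as written, the first gives verum or sham status to a GP who has no need of it and who advises on medication in all arms. The second sends arm-revealing data to analysts whom Design describes as blinded. The named reference groups add to the second.

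The size of any resulting bias cannot be derived. Background credits prophylaxis with a 50% reduction in attack frequency, but turning that into migraine days would need a between-arm difference in prescribing and a baseline number of migraine days, and the document gives neither. The 14% figure is an upper bound under the assumption in step 5 and is context only. The conclusion rests on reading the doctor who is told as the GP, and on the points and techniques fields being among the DRB variables that pass to the CRDD.

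**What to change.** 1. Reconcile Randomisation and treatment allocation with Data compilation: the verum/sham code goes only to the acupuncture physician, and the GP is told only that the patient has acupuncture or conventional treatment.
2. Keep needling points, techniques and TCM treatment data in a separate treatment log held by the acupuncture physician, withheld from the assessor and the analysis centre until database lock. State that these fields are not part of the CRDD until then.
3. In Statistical analysis, use neutral group codes and produce all pairwise contrasts. Apply the sham and group C reference labels only after unblinding.

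The cost is a revised phone and fax script and a split record form, with no extra staff or visits. The change is not a remedy for predictability within blocks. Under the assumption in step 5, someone told only acupuncture or conventional could still foresee which of the two comes next for Σ[C(6,k) + C(3,k)]/C(9,k) = 1.5 + 0.43 = 1.93 of 9 patients, but could not tell verum from sham.
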